#### Social prescribing link workers [SPLW]

2.8.1

If the SPLW plans or makes a connection to, and/or the individual referred expresses an interest in attending, a local physical activity, they are eligible for recruitment and they will be informed about the study. This can occur at the time of referral, the first appointment or subsequent appointments. If the potential participant is agreeable, the SPLW will give them a participant information leaflet and informed consent form (study information) and ask consent to share their contact details with the research team. Following a seven-day period, the research team will then contact those who agree to be contacted to screen for eligibility and obtain verbal and written consent to participate, or participants can contact the research team directly.

#### Local sports partnership community sports development officers [LSPO]

2.8.2

LSPO meet with individuals for the first time at the initial session of a local sports partnership physical activity programme, or during a screening phone call. Every person that the LSPO meets at these initial sessions or during phone calls during the recruitment period will be informed about the study. If the potential participant is agreeable, the LSPO will then give them the study information and ask consent to share their contact details with the research team. The research team will then contact those who agree to be contacted directly after seven days to screen for eligibility and obtain verbal and written consent to participate, or participants can contact the research team directly.

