### Sample

2.5

Participants will be those who are referred or self-referred to a social prescribing link worker or local sports partnership community sports development officer and who undergo an intervention delivered by an intermediary i.e., undergo assessment, onward connection to local physical activities and follow-up. A baseline assessment will be taken upon enrolment on to the study, and this assessment will be repeated after 12 weeks from time of enrolment.

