#### International Physical Activity Questionnaire - Short Form

2.9.2

The International Physical Activity Questionnaire is a self-reported measure of multiple domains of physical activity, such as physical activity undertaken for leisure, work, transport and/or domestic activities [45]. There are two versions, the long form and short form (IPAQ-SF). The original authors of the questionnaire recommend the IPAQ-SF, as it is less burdensome for both participants to complete and researchers to administer. This was an important consideration due to the remote nature of this proposed study (See Section 2.10 ‘Data Collection’). The IPAQ-SF assesses physical activity behaviour over the last seven days and includes measures of frequency and duration of vigorous physical activity, moderate physical activity, walking and sedentary behaviour. Using a standardised scoring protocol, total days of activity, total activity (minutes/week), metabolic equivalent minutes per week and physical activity category (low, moderate or high levels of physical activity) can be calculated [46].

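### Baseline is not anchored before the first activity session, so the week 0 to 12 change mixes pre-start and post-start baselines

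*Protocol article*

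**What the plan says.** **Design and intervention.** Section 2.4 of the protocol article sets a before-and-after comparison without a control group. Section 2.1 counts attending and taking part in the local activity as the second phase of the intervention.

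**Baseline.** Section 2.5: "A baseline assessment will be taken upon enrolment on to the study". Follow-up (T1) comes 12 weeks after enrolment. Neither time point is tied to the first activity session.

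**Sports partnership (LSPO) clients.** Section 2.8.2 states: "LSPO meet with individuals for the first time at the initial session of a local sports partnership physical activity programme". The same sentence gives a telephone screening as the other possible first contact. They hear of the study on that occasion. The next step is: "The research team will then contact those who agree to be contacted directly after seven days to screen for eligibility". Consent is taken at this stage too. As an alternative to waiting, "or participants can contact the research team directly".

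**Social prescribing (SPLW) clients.** Under section 2.8.1 a client can be recruited when a connection is planned, already made, or only of interest. On timing: "This can occur at the time of referral, the first appointment or subsequent appointments". The same seven-day wait and the same direct-contact option apply.

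**Measures.** Section 2.9.2: "The IPAQ-SF assesses physical activity behaviour over the last seven days". Item #10 of the data collection form asks for the types of exercise done at present. Table 2 uses change in item #10 for objective v, and change in IPAQ-SF, SEE, SWEMWBS and self-rated health for objective viii.

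**The concern.** With no control group, T0 is the only comparator. Where a participant has already attended, T0 is an early on-programme value and not a pre-intervention one. If the first sessions raise activity, self-efficacy or wellbeing, part of the gain sits in the baseline and drops out of the T0 to T1 difference. On item #10 the new activity can already be listed at T0, so its uptake does not register as a change.

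This matters beyond the effect estimate. Section 2.9.1 says the questionnaires are being tried out as outcome measures for later effectiveness studies. A late baseline could make a responsive instrument look unresponsive. Because the position of T0 varies by recruitment route, it may also differ systematically between the two services. Any contrast in change between them would then partly reflect when baseline was taken.

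**Working it through.** **1. Timeline for an LSPO client approached at the initial session.** Call that session day 0.

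- Default route: the team makes contact from day 7, so T0 is on day 7 or later. The IPAQ-SF window for T0 on day 7 is days 0 to 6, which has no pre-session days.
- Direct-contact route: T0 may fall on some day k below 7. The window is days k − 7 to k − 1 and holds 7 − k pre-session days. For k = 3 it covers days −4 to 2, that is, four days before the session and three from the session onwards. T0 still follows the start.
- Follow-up on the default route: 7 + 84 = 91 days, or 13 weeks after the first session. The contrast is about 1 week against about 13 weeks of exposure.

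**2. Other routes.**

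| Route | T0 relative to first session |
|---|---|
| LSPO, initial session | Always after |
| LSPO, screening call | May be before |
| SPLW, connection planned or of interest | May be before |
| SPLW, connection already made | Before or after; a connection is not yet attendance |

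**3. Plan figures.** The target of 30 reproduces as 3 outcome measures × 10 participants, split about 15 and 15 (section 2.7). The protocol gives no split by recruitment route, and no effect size, SD, alpha or power for the change analysis. What follows is illustration on assumptions.

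**4. Attenuation.** Let Δ be the true mean change (taken as equal in both groups), f the share already started at T0, and s the share of their gain already present at T0.

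Observed mean change = (1 − f)Δ + f(1 − s)Δ = Δ(1 − f·s)

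| f | s = 0.25 | s = 0.5 | s = 1.0 |
|---|---|---|---|
| 0.25 | 0.938 | 0.875 | 0.75 |
| 0.5 | 0.875 | 0.75 | 0.50 |
| 0.75 | 0.812 | 0.625 | 0.25 |
| 1.0 | 0.75 | 0.50 | 0.00 |

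At f = 0 the ratio is 1. The row f = 0.5 would correspond to all 15 LSPO participants having started and no SPLW participant.

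**5. Consequence for the paired t-test (section 2.11).** Assume n = 30, two-sided 0.05, a true standardised change of 0.5 and an SD of change unaffected by the timing. Noncentrality is 0.5 × ratio × √30, and power comes from the noncentral t distribution.

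| Ratio | Noncentrality | Power |
|---|---|---|
| 1.00 | 2.74 | 75% |
| 0.875 | 2.40 | 64% |
| 0.75 | 2.05 | 51% |
| 0.50 | 1.37 | 26% |

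**The case against.** The strongest reply is that the problem is confined to one route and is partial even there.

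- **How many.** A reader might infer that most participants have a late baseline. The documents do not support this. Screening calls and planned or interest-only SPLW connections can precede any session, and no split is given. The figure of 15 LSPO participants is a ceiling for that service.
- **How late.** A reader might infer a fixed gap of at least seven days. Seven days is the default only, because participants may contact the team directly with no stated minimum wait.
- **How much.** A reader might infer that the intervention is simply compared with itself. On the default route about one week of exposure precedes T0, so attenuation is usually partial. Nothing shows that SEE or SWEMWBS would move materially after one session.
- **Which direction.** Late T0 pulls towards no change if early sessions help. Without a control, regression to the mean and self-report can push towards apparent improvement, so the net bias is uncertain.
- **Safeguards.** Gatekeeper logs date each contact (section 2.9.7), interview item #3 asks which activities were accessed, items #7–9 ask whether the measures captured improvement, and gatekeeper interviews cover recruitment timing (section 2.9.8).

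All four limits on size and direction stand. The safeguards help only in part. The logs record contacts with the intermediary, not first attendance. Item #3 serves objective v and leaves the questionnaire scores as they are. The interviews can describe the timing but cannot restore a baseline. The limitations in section 3 name the pilot nature of the study and not the timing of T0.

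**Conclusion.** The point holds in a limited form. T0 is not anchored before the first session. For LSPO clients approached at that session it always falls after the activity has begun, by about seven days or more on the default route. Some SPLW clients with a connection already made may be affected too. The pooled week 0 to 12 change therefore mixes two kinds of baseline and probably understates change for those already started, provided that early sessions raise scores.

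The size cannot be derived from the protocol. With half the sample started and 25% to 100% of their gain present at T0, observed change is 88% to 50% of true change. All of the change disappears only if every participant has started and the whole gain is present at T0, which nothing in the document suggests. A claim that the study is biased overall towards no change would go too far.

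Severity: should-fix. Change is one of eight objectives in a feasibility study that already limits its conclusions on effectiveness. Later analysis cannot separate the two groups, however, unless the start date is collected.

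**What to change.** 1. Where a screening call or sign-up step exists, give the study information then and complete T0 before the first session.
2. Add two fields to the T0 form: the date of the first activity session (or not yet started) and the number of sessions attended so far.
3. Report week 0 to 12 change separately for participants not started and already started at T0. Treat only the former as the before-and-after result, and label the latter as change from an on-programme baseline. Do the same for item #10.
4. State in the limitations that T0 follows the start of the activity for some participants, and how many.

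Do not re-anchor the IPAQ-SF to the week before the first session. That departs from the instrument's last-seven-days recall, mixes recall windows, and alters the tool whose suitability objective vii is testing.

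Cost: two form fields, one stratified table, and some extra work for services that the protocol describes as often lacking administrative support. Earlier hand-out is not possible for clients first met at the session. The subgroups will be small and imprecise, so they should be reported descriptively. The start date is best captured prospectively, so the fields should be added as early in enrolment as possible.

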### Outcomes

2.9

Definitions of outcomes, measurement tools, and time points for data collection are summarised in Table 2.

**Table 2 tbl2:** *Data Methods and Schedule of Measures.* Study objectives, descriptions of their associated measures, data measurement tools and the timeframe of data collection. Abbreviations: Short Warwick-Edinburgh Mental Well-being Scale (SWEMWBS), Self-Efficacy for Exercise Scale (SEE), International Physical Activity Questionnaire - Short Form (IPAQ-SF), Numerical Rating Scale (NRS).

Objectives	Measure Definition	Measurement Tool	Data Collection Timeframe		
			Time 0	Time 1 (12 Weeks)	Post-recruitment period
i To determine the rate of recruitment and enrolment to the proposed study of individuals who undergo an intervention delivered by an intermediary, which includes participation in local physical activities (intervention participants).	How many people are approached/receive information about the study from the gatekeeper - # (%) of total clients referred to an intermediary who will be connected to local physical activities i.e., eligible people - # (%) of eligible people who receive study information How many eligible people take part in the study - # (%) eligible people who receive study information who take part in the study	Gatekeeper recruitment log Gatekeeper recruitment log	Ongoing throughout recruitment period Ongoing throughout recruitment period		
ii To examine the suitability and acceptability of recruitment methods to the proposed study.	How long it takes to recruit 3–4 people from each service/gatekeeper - length of recruitment period per service (days) Reasons given for not taking part - frequency count of reasons given for not taking part in research Explore gatekeepers' perceptions of how open clients were to take part in the research, their experience of recruitment and the acceptability of the recruitment methods.	Gatekeeper recruitment log Gatekeeper recruitment log Gatekeeper semi-structured interview items #1-8	Ongoing throughout recruitment period Ongoing throughout recruitment period		**✘**
iii To determine retention to the proposed study.	How many people return for a follow-up assessment with the research team	# (%) of participants who return for 12-week follow-up assessment		**✘**	
iv To describe the demographic and health characteristics of intervention participants.	The age, gender, marital status, urban/rural, level of education, ethnicity, employment status, self-reported presence/absence of chronic condition, self-reported rating of health, and types of exercise currently undertaken of the study sample	Data collection form items #1-10	**✘**	**✘** (Items #9–10 only)	
v To determine participation in and adherence to local physical activities by intervention participants.	Changes in types of exercise undertaken by participants from Week 0 to Week 12 - including self-directed physical activity and/or local physical activities accessed as a result of the intervention	Data collection form item #10 - *“What types of exercise do you do currently? Please provide a list.”* Intervention participant semi-structured interview item #3 - Includes prompts about what local physical activities were accessed as a result of the intervention, and adherence to the local physical activity	**✘**	**✘** **✘**	
vi To explore the acceptability of the intervention delivered by the intermediary.	Explore intervention content and delivery by the intermediary, the impact of the support provided, and how acceptable the intervention was to the participant.	Intervention participant semi-structured interview items #1–6, 11 Intervention acceptability NRS (Intervention participant semi-structured interview item #10)		**✘** **✘**	
vii To explore suitability, acceptability and completion rates of the measurement tools by intervention participants.	Determine if the outcome measures used in this proposed study captured important information/improvements made by the participant, the rates of completion of each outcome measure, and explore experience of completing the outcome measures.	Intervention participant semi-structured interview items #7-9 # (%) items completed in data collection form items #1–10, SWEMWBS, SEE, IPAQ and intervention participant semi-structured interview items #1-11	**✘**	**✘** **✘**	
viii To assess if change occurs in physical activity and health-related outcomes following participation in the intervention.	Change in IPAQ-SF score from Week 0 to Week 12 Change in SEE score from Week 0 to Week 12 Change in SWEMWBS score from Week 0 to Week 12 Changes in self-rated rating of health from Week 0 to Week 12	IPAQ-SF SEE SWEMWBS Data collection form item #9	**✘** **✘** **✘** **✘**	**✘** **✘** **✘** **✘**	

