#### Gatekeeper recruitment logs

2.9.7

Gatekeepers will be asked to keep a record of how many clients they had contact with during the recruitment period, how many people were approached about the study, and the reasons for refusal to take part in the study. This record will be kept until 3–4 participants have been recruited from each participating service. For participants recruited to the study, gatekeepers will also be asked to keep a record of their contacts with this person (date, length of each contact and mode of contact). This will help to verify the data collected from participants in their interview.

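### Table 2 bases approach and uptake rates on receipt of study information, which only already agreeable clients are given, so refusals at first mention are misplaced in both rates

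*Protocol article*

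**What the plan says.** Table 2 in section 2.9 sets two rates for objective i that matter here, both taken from the gatekeeper recruitment log.

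- The approach rate sits under the heading "How many people are approached/receive information about the study from the gatekeeper" and is the number and percentage "of eligible people who receive study information".
- The uptake rate is the number and percentage of "eligible people who receive study information who take part in the study".

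Section 2.8 describes recruitment in two steps, on both routes.

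- Social prescribing link workers (2.8.1): once a connection to a local activity is planned or made, or the person shows interest in one, "they are eligible for recruitment and they will be informed about the study". Then: "If the potential participant is agreeable, the SPLW will give them a participant information leaflet and informed consent form (study information". The bracketed label defines the term that Table 2 uses.
- Local sports partnership officers (2.8.2): "Every person that the LSPO meets at these initial sessions or during phone calls during the recruitment period will be informed about the study". Then: "If the potential participant is agreeable, the LSPO will then give them the study information".

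Section 2.9.7 lists what the log holds: clients in contact during the recruitment period, "how many people were approached about the study", and reasons for refusal. It does not list a count of people given study information.

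**The concern.** Table 2 treats being approached and receiving study information as one event. Section 2.8 separates them by a filter, the client's first yes or no. Someone who says no when told never gets the leaflet. Applied as written, Table 2 records that person as not approached and leaves them out of the uptake denominator, although objective ii wants the same person's reason for refusing.

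Recruitment and enrolment is the first objective. Section 2.11 sets no progression criteria and expects the findings to inform later research and trial design, so the reported rates themselves are what a later planner would use. Gatekeepers not raising the study and clients turning it down call for different remedies. The rates as defined shift losses from the second cause to the first.

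**Working it through.** The protocol states no expected approach or uptake rate, so there is no figure of its own to reproduce.

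**Notation.** E = eligible people; A = eligible people told about the study; a = share of A who are agreeable; R = a × A = people given study information; n = participants. The target n = 30 is from section 2.7. The documents do not give E, A or a; E = 120, A = 100 and the range of a are assumptions for illustration.

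**Formulas.**

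- Uptake as written: n/R = n/(a × A) = (n/A)/a. It exceeds uptake per person told by the factor 1/a.
- Approach rate as written: R/E = a × (A/E). It is the true approach rate multiplied by a.
- Product of the two: (n/R) × (R/E) = n/E, which does not contain a.

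**Numbers.** Per person told, uptake is 30/100 = 30.0% and the approach rate is 100/120 = 83.3%, whatever a is. As written:

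| a | R | Uptake n/R | Factor 1/a | Approach rate R/E | n/E |
|---|---|---|---|---|---|
| 1.0 | 100 | 30.0% | 1.00 | 83.3% | 25.0% |
| 0.9 | 90 | 33.3% | 1.11 | 75.0% | 25.0% |
| 0.75 | 75 | 40.0% | 1.33 | 62.5% | 25.0% |
| 0.6 | 60 | 50.0% | 1.67 | 50.0% | 25.0% |
| 0.5 | 50 | 60.0% | 2.00 | 41.7% | 25.0% |
| 0.4 | 40 | 75.0% | 2.50 | 33.3% | 25.0% |

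A planner who took the written uptake as a rate per approach would, at a = 0.6, expect to need 30/0.50 = 60 approaches for 30 participants, where 30/0.30 = 100 were made.

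**A check that needs no assumed value.** Section 2.8 has eligible link-worker clients, and everyone an officer meets, told about the study. If gatekeepers follow this, A/E among those people is about 1 and the written approach rate reduces to a. Any shortfall below 100% would then be client refusal, reported under a heading about how many were approached.

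**The case against.** The strongest reply is that Table 2's heading pairs being approached with receiving information about the study, so the lines beneath it may simply mean people told. The log supports this: it lists people approached and no count of leaflets, so the count actually available may be the right one. On that reading the bias vanishes. This reading is possible, but it overrides the label that 2.8.1 gives the leaflet and consent form. It also leaves Table 2 naming a quantity that its stated source does not list. With eleven services keeping logs (section 2.8), different gatekeepers could count different events. The wording needs reconciling either way.

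Other points stand and limit the concern.

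- Overall yield is unchanged. A reader might infer that the study will overstate how many eligible clients end up enrolled. It will not, because the two errors cancel in n/E.
- No data are lost on what the log is said to hold. The number approached and the reasons for refusal are both recorded.
- The size is entirely assumed. Being agreeable may screen out few people or many.
- Uptake among people given the leaflet is a legitimate staged measure. The fault lies in using it as the only uptake rate and in equating its denominator with people approached.
- Putting the log's approached count straight into the denominator would not be clean. Officers tell everyone they meet, the research team screens for eligibility later, and 2.9.7 does not limit the count to eligible people. That could understate uptake.

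**Conclusion.** The point holds on the protocol's own defined term. Once a single eligible person declines on being told, the uptake rate in Table 2 is too high by 1/a and the approach rate is too low by the factor a. For an assumed a of 0.9 to 0.4, uptake is 1.1 to 2.5 times the rate per person told; the documents give no basis for choosing within or outside that range. What is misreported is the stage at which people were lost, not the overall yield. A claim of large, known inflation, or of a wrong overall recruitment rate, is not supported. This is a definition that should be corrected before the rates are reported. It does not threaten the conduct of the study.

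**What to change.** In Table 2, objective i:

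1. Define the approach rate as eligible people told about the study divided by eligible people.
2. Define uptake as participants divided by eligible people told about the study.
3. Report the number given study information who agreed to be contacted as a separate intermediate step, so that the sequence reads eligible, told, given information and agreed to contact, enrolled.
4. Take the counts from the gatekeeper log in 2.9.7, with the approached count limited to people who meet Table 2's definition of eligible. Where eligibility is unknown, as it may be for people told by the officers before screening, show that number separately.

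Use the same terms in 2.8.1, 2.8.2, 2.9.7 and Table 2. The cost is some rewording, one extra count in the log, and a headline uptake that will be lower than on the present definition if anyone declines when told.

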To date, the research team have completed a scoping review of the published literature to describe the processes of an intermediary when connecting community-dwelling individuals to local physical activities [14]. This review found many different approaches to establishing this connection, and often the processes of referral, assessment, follow-up, and discharge were poorly described. In order to address these gaps, a qualitative descriptive study was carried out where intermediaries from three different professions across Ireland were interviewed; health promotion and improvement officers, local sports partnership community sports development officers and social prescribing link workers [15]. The aim of this study was to gain insight into the role of intermediaries in Ireland and to further define the processes, practices and procedures in the Irish context.

The two previous studies helped to determine the processes of the ‘intervention’ delivered by an intermediary, i.e., receive a referral or self-referral, conduct an assessment, connect to a local physical activity, followed by a period of follow-up and subsequent discharge from the intermediary service. Based on the results from the scoping review and the qualitative descriptive study, there remained three main evidence gaps: 1) after the individual connects to local physical activities, do they continue to engage in physical activity, 2) what are the perspectives and experiences of individuals referred to an intermediary, and 3) is an intervention delivered by an intermediary effective in improving physical activity and wider health-related outcomes? However, to date there has been a limited number of high-quality studies investigating the effectiveness of the intervention delivered by an intermediary, with only five RCTs identified in the scoping review [[16], [17], [18], [19], [20]].

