### Aims and objectives

2.2

Feasibility is defined as the extent to which a task or innovation can be successfully carried out within a given agency or setting and performed relatively easily or conveniently given existing resources and circumstances [33]. The aim of this proposed study will be to investigate the feasibility of an intervention delivered by an intermediary to improve physical activity and health-related outcomes of community-dwelling adults. Specific objectives include.i.To determine the rate of recruitment and enrolment to the proposed study of individuals who undergo an intervention delivered by an intermediary, which includes participation in local physical activities (intervention participants).ii.To examine the suitability and acceptability of recruitment methods to the proposed study.iii.To determine retention to the proposed study.iv.To describe the demographic and health characteristics of intervention participants.v.To determine participation in and adherence to local physical activities by intervention participants.vi.To explore the acceptability of the intervention delivered by the intermediary.vii.To explore suitability, acceptability, and completion rates of the measurement tools by intervention participants.viii.To assess if change occurs in physical activity and health-related outcomes following participation in the intervention.

The CONSORT extension to pilot and feasibility trials, and the SPIRIT guidelines for protocols of interventional trials have been used to guide the reporting of this protocol [[34], [35], [36]].

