### Data analysis

2.11

Quantitative data analysis will be performed using SPSS V28 (IBM, USA) and Microsoft Excel software (Microsoft Corporation, USA). Categorical variables (counts and proportions) and graphical representations e.g., bar charts will be used to present feasibility outcomes. Summary statistics for continuous variables will also be presented as (i) means and standard deviations for normally distributed data, and (ii) median and interquartile ranges for data which was not normally distributed. Within-group differences will be assessed using paired T-tests for normally distributed data and Wilcoxon signed rank tests for data which are not normally distributed.

A qualitative descriptive approach will be taken to the analysis of the exit interviews and free text responses, with the aim of providing a rich, straight description of an experience or an event close to the participant's language [39]. Interviews will be digitally recorded and transcribed verbatim. Transcripts will be analysed using an inductive qualitative content analysis as described by Elo & Kyngäs [55]. Themes will be developed in a four step approach; initialization, construction, rectification and finalization [56]. One researcher [[name]] will analyse all transcripts using NVivo 14 (QSR International, Australia). The qualitative and quantitative data will then be integrated to provide a comprehensive analysis [37,57].

Progression criteria were not developed for this proposed study, as guidance regarding the application and development of progression criteria for non-randomised feasibility trials is limited [58,59]. In addition, progression criteria are generally used to decide whether to progress a feasibility trial to a definitive controlled trial [60]. It is not yet clear whether a controlled or experimental trial will be the most appropriate methodology for the next phase of this research. By examining feasibility and acceptability of the evaluation design in this proposed study, it is anticipated this will inform future research and trial design.

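### Objective v sets out to determine participation and adherence, but its measure in Table 2 is a change in a free list of exercise types, which records neither attendance nor persistence

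*Protocol article*

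**What the plan says.** Section 2.2 gives objective v as "To determine participation in and adherence to local physical activities by intervention participants". In Table 2 (Section 2.9) the measure definition for that objective is "Changes in types of exercise undertaken by participants from Week 0 to Week 12", with the scope "including self-directed physical activity and/or local physical activities accessed as a result of the intervention".

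Two tools are listed against it:

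- Data collection form item #10, at T0 and T1: "What types of exercise do you do currently? Please provide a list".
- Participant interview item #3, at T1 only: "Includes prompts about what local physical activities were accessed as a result of the intervention, and adherence to the local physical activity".

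Section 2.11 states how each kind of data will be handled. For feasibility outcomes: "Categorical variables (counts and proportions) and graphical representations e.g., bar charts will be used to present feasibility outcomes". For interviews: "Transcripts will be analysed using an inductive qualitative content analysis".

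**The concern.** The verb in objective v is the one used for recruitment and retention (objectives i and iii), both of which have a # (%) measure in Table 2. Objective v has none, and adherence does not appear in its measure definition at all. The definition tracks which kinds of exercise a person names, and it pools exercise done independently with the activity that the intermediary arranged.

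This matters because Section 2.1 makes attendance and participation in the local activity the second of the intervention's two phases. A feasibility study should be able to say how many enrolled people reached that phase and how many were still in it at 12 weeks. The next study would need those two figures for planning, and the defined measure supplies neither.

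**Working it through.** The plan states no figure for this objective, so there is nothing to reproduce. The check is whether any planned data source yields a count of attendance or persistence, and what the defined measure returns in simple cases.

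**Step 1. Sources of attendance data**

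| Source | Where | What it records | Gives an attendance or persistence count? |
|---|---|---|---|
| Form items #1–10 | Table 2, row iv; Section 2.9.1 | Ten variables for ten items: age, gender, marital status, urban/rural, education, ethnicity, employment, chronic condition, self-rated health, exercise types. Only #9–10 are repeated at T1 | No |
| Interview item #3 | Table 2, row v; Section 2.9.5 | Prompts on activities accessed through the intervention and on adherence | Not as defined: no count, denominator or threshold |
| Gatekeeper log | Section 2.9.7 | Date, length and mode of contacts between intermediary and participant | No: contacts, not sessions |
| IPAQ-SF | Section 2.9.2; Table 2, row viii | All physical activity in the previous seven days | No: not specific to the arranged activity |

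**Step 2. What a change in listed types returns**

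| Participant | Listed at T0 | Listed at T1 | Change in types |
|---|---|---|---|
| A: in a walking group, attends every session | walking group | walking group | none |
| B: same group, attends rarely but still counts it as current | walking group | walking group | none |
| C: never attends the arranged activity, takes up home exercise | nothing | home exercise | gain |
| D: attends the arranged class for much of the period, then stops | nothing | nothing | none |
| E: never attends anything | nothing | nothing | none |

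A and B differ in adherence and get the same result. D and E differ in participation and get the same result, because the item asks about current exercise and D would properly leave the class off. C shows a gain without any participation. These cases are illustrative; they need no assumption about the number of sessions.

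**Step 3. Can the activity already be on the T0 list?**

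Under Section 2.8.2, local sports partnership officers may first meet people at the opening session of a programme, and the research team makes contact seven days later. Baseline is taken on enrolment (Section 2.5), so the activity may already be listed at T0, and a participant who then attends throughout shows no change. This does not hold for everyone. The same section allows recruitment by screening call, and Section 2.8.1 allows social prescribing clients to be recruited when a connection is only planned.

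**Step 4. Measure against reporting rule**

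Section 2.11 promises counts and proportions for feasibility outcomes. For objective v the only defined count that could be formed is of people whose list of types changed. By Step 2 that is a count of neither participants nor adherers.

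**The case against.** The strongest reply is that objective v has two tools, and the second asks directly about adherence and about activities accessed because of the intervention. In a mixed-methods study with a target of 30, asking each interviewee what they took up would allow a count, and would separate arranged from self-directed activity. The wording of the prompts belongs to the topic guide in Fig. 2, which could not be read here, so questions on frequency or continued attendance cannot be ruled out. Section 2.9.7 adds that gatekeeper contact records will help verify interview accounts, and intermediaries sometimes attend sessions with clients (Sections 2.1.1 and 2.1.2).

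Much of this stands. A reader might infer that adherence goes uncollected, or that the study can establish nothing about participation. The documents do not support that. What remains is that the interview is flexible, reaches only those who complete it at 12 weeks, is planned for inductive content analysis, and has no stated count or denominator. For acceptability, by contrast, the protocol adds a 1–10 rating inside the same interview (Section 2.9.6); adherence gets no such item.

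Three other strong readings also fail:

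- **That a class tried once and dropped would score as a gain.** Item #10 asks about current exercise, so it should not be listed.
- **That the first evidence gap in the Introduction goes unanswered.** That gap asks "after the individual connects to local physical activities, do they continue to engage in physical activity", meaning physical activity in general, and the IPAQ-SF at both time points bears on it.
- **That the study fails because change cannot be related to exposure.** No objective in Section 2.2 seeks such an analysis.

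It might also be said that a fuller protocol or an analysis plan could settle the matter. However, the article quotes item #10 in full and accounts for all ten form items, and an analysis plan cannot recover data that were not collected.

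**Conclusion.** The point holds in a limited form. The measure defined for objective v does not measure what the objective names, and the source that does touch adherence has no defined numerical output. Followed as written, the plan gives a description of exercise types and interview accounts, but no defined participation or adherence proportion.

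One of eight objectives is affected. Recruitment, retention, completion rates and the before-and-after comparisons are untouched, so this should be corrected but does not undermine the study. There is no numerical error to size.

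The conclusion assumes that the form contains only the ten items listed, and that interview item #3 is handled as Section 2.11 says. If the topic guide already contains fixed questions on attendance put to everyone, what remains is to define the measures and state their denominators in Table 2.

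**What to change.** Add short structured items at T1, asked of every participant, including those who complete forms by post:

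1. Which local activity the intermediary arranged.
2. Attended it at least once (yes/no).
3. Still attending at 12 weeks (yes/no, with reason if not).
4. Approximate number of sessions attended and, where the activity is scheduled, the number offered.

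In Table 2, define participation as at least one session attended, and adherence as still attending at 12 weeks. Use sessions attended divided by sessions offered only as a supplement, where a denominator exists: Section 2.1.2 includes gyms and gardening, for which sessions offered may have no natural meaning.

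Report # (%) with all enrolled as the denominator for participation, state the denominator for adherence, and show how many have no T1 data. Present results overall and, descriptively, by service type. With about 15 per service, one participant is 1/15 = 6.7 percentage points, so no comparison between services should be read into them. Keep item #10 as description and interview item #3 as explanation of the figures.

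The cost is a few items on an existing form, hence slightly more participant burden. The data remain self-reported.
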